### Phase IV: implementation

During the final phase, the conditions for large-scale implementation will be defined using the results from phase III. Barriers and facilitators to implementation and potential adverse effects will be determined. For further implementation, local stakeholders and national GP organisations will be involved to integrate the use of the TOOL-kit in daily general practice.

## Analysis

### Surveys (phase I)

The results of our GP survey will be compared to the results of our patient survey using descriptive statistics (sum, mean, standard deviation). Furthermore, the results will be compared to the earlier performed survey studies by [name] et al. [5, 6] using ANOVA and t-test or Kruskall-Wallis ANOVA and Mann-Whitney U tests depending on normality of the data. Associations will be tested using linear regression analysis. All data will be analysed using SPSS (version 26.0).

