#### GP and patient surveys

Surveys will be used to investigate patients’ and GPs’ views on personal continuity to determine relevant components of the intervention. The surveys will contain questions regarding GPs’ and patients’ views on personal continuity, factors influencing personal continuity and their suggestions on how to improve personal continuity in general practice. Both questionnaires will be based on previous research by [name] et al. [5, 6]. and the results of the literature study performed in phase 0.

For the patient survey, we will recruit 35 GPs from general practices in two regions in the Netherlands and instruct them to take a random sample of 30 patients aged 65 years and older from the electronic medical record (EMR) (*n* = 35*30 = 1050). The selected patients will receive a postal survey with an accompanying letter from their GP. For the GP survey, we will randomly select 100 GPs for participation through various local GP networks. The GPs will receive a digital survey through Survalyzer: an online program for distributing, collecting and analysing surveys [59].

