#### Trial (phase III)

Descriptive statistics will be used to summarize population characteristics. For the primary analysis, the mean NCQ score at baseline and at 12 months follow-up will be compared using a linear mixed model with a random effect for practice and a fixed effect for time point. To analyse if differences depend on longer exposure to the TOOL-kit, the main effect of wedge number and the two-way interaction between wedge number and time point will be determined.

Secondary outcomes measures from the surveys will be compared before and after the intervention and between measurements on different time points using mixed linear models or generalized estimating equations depending on the type of outcome measure. This accounts for clustering of participants within the practices. For outcomes that are collected in more than two periods, the length of exposure to the TOOL-kit main determinant will be considered using the control condition as a reference. A two-sided significance level of 5% will be used for all analyses.

The semi-structured telephone interviews will be analysed according to the framework method described in the *focus groups* section.

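### The phase I patient survey is sampled by GP but tested as if patients were independent, so p-values against the earlier surveys and for GP-level covariates are too small

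*Protocol article*

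**What the plan says.** The protocol article, under GP and patient surveys, sets up a two-stage sample for the patient survey: "we will recruit 35 GPs from general practices in two regions in the Netherlands", and then "instruct them to take a random sample of 30 patients aged 65 years and older". The article gives the total as 35 × 30 = 1050 patients invited. The GP survey is separate: "we will randomly select 100 GPs for participation through various local GP networks".

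Under Analysis, Surveys (phase I), three things are planned:

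- GP and patient results are set beside each other with descriptive statistics only.
- Results are compared with earlier survey studies "using ANOVA and t-test or Kruskall-Wallis ANOVA and Mann-Whitney U tests depending on normality of the data".
- "Associations will be tested using linear regression analysis".

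No random effect, generalized estimating equation, robust standard error or survey-design correction is named for phase I. The significance level appears under Trial (phase III) but is worded broadly: "A two-sided significance level of 5% will be used for all analyses". That same section gives the phase III primary outcome a random practice effect, and it uses mixed models or generalized estimating equations for the secondary outcomes in order to allow for clustering.

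**The concern.** The survey asks about views on personal continuity, which the Background section defines through having a personal provider. Patients sampled from one GP share that provider, so some positive correlation within GP is a reasonable expectation, although the article does not quantify it. Each named test takes its standard error, or its rank-based null distribution, from independent observations. The only stated criterion for choosing among them is normality, which does not address dependence.

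At stake are two kinds of phase I claim: that patients' views have changed since the earlier surveys, and that some GP or practice characteristic is associated with those views. Both would be called significant more often than the stated 5%.

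**Working it through.** **Inputs from the article.** 35 GPs; 30 patients sampled per GP; two-sided 5% level. The stated total reproduces: 35 × 30 = 1050.

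**Assumptions.** The article gives no ICC, so 0.02 and 0.05 are assumed. It gives no phase I response either. Two cluster sizes m are used: 30 (everyone responds), and 30 × 0.35 = 10.5, which borrows the 35 responders per 100 approached that the Sample size section expects in phase III.

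**Formulas.** Design effect DE = 1 + (m − 1) × ICC. Effective n = 35m / DE. The naive standard error is too small by a factor √DE. The true error of a nominal 5% test is 2 × [1 − Φ(1.96/√DE)] when all the variance of the contrast is clustered. Against an unclustered comparator of equal size, DE is replaced by (DE + 1)/2.

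| m | ICC | DE | Effective n | √DE | True error, fully clustered | True error, equal-sized unclustered comparator |
|---|---|---|---|---|---|---|
| 10.5 | 0.02 | 1 + 9.5 × 0.02 = 1.19 | 309 of about 368 | 1.09 | 7.2% | 6.1% |
| 10.5 | 0.05 | 1 + 9.5 × 0.05 = 1.48 | 249 of about 368 | 1.21 | 10.7% | 7.8% |
| 30 | 0.02 | 1 + 29 × 0.02 = 1.58 | 665 of 1050 | 1.26 | 11.9% | 8.4% |
| 30 | 0.05 | 1 + 29 × 0.05 = 2.45 | 429 of 1050 | 1.57 | 21.1% | 13.6% |

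**Regression, by simulation.** There were 4000 runs of 35 GPs × 30 patients with no true association, analysed by linear regression without a clustering term.

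| ICC | Rejections, GP-level covariate | Rejections, patient-level covariate that does not vary by GP |
|---|---|---|
| 0.02 | 12.8% | 5.2% |
| 0.05 | 20.5% | 4.6% |

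The GP-level column agrees with the formula (11.9% and 21.1%). The patient-level column stays at the nominal 5%, so the problem is confined to covariates that differ between GPs or practices.

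**The case against.** The strongest defence is that this is formative work in a condensed article and that nothing hangs on a p-value. Much of that stands. A reader might infer that falsely significant results decide which components enter the TOOL-kit, but the documents do not support this. Focus groups discuss the survey results to prioritise components. The Delphi study then decides by ratings of effectiveness and feasibility, with 75% consensus and after that a majority vote. No significance threshold enters either step.

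It is also fair to say that the size of the error cannot be pinned down. The ICC and phase I response are not given, and the design and size of the earlier surveys cannot be seen from the article. The upper figures need every invited patient to respond and a comparator as clustered as the new survey. The article names no regression covariates, so how many associations are affected is unknown.

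The argument that clustering may be left to a fuller document does not stand. The article does not leave the phase I tests open. It names them, and they do not match the sampling it describes. It also says so where it does intend to allow for clustering, in phase III.

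**Conclusion.** The mismatch is real but limited. For any positive within-GP correlation, p-values are too small for the patient survey against the earlier surveys, and for covariates that vary by GP or practice. Assuming an ICC of 0.02 to 0.05, the true error of a nominal 5% test on a fully clustered contrast is about 7-11% at 35% response and 12-21% at full response. Against an equal-sized unclustered comparator it is lower: about 6-8% and 8-14%. An ICC near zero would make the issue negligible.

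The wider reading, that every phase I result is too optimistic, goes too far. Regression on purely patient-level covariates holds its level, the GP survey is not clustered by GP, and the GP-versus-patient comparison involves no test. The phase III primary analysis is untouched. This is a low-priority correction.

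**What to change.** In Surveys (phase I), state that patient-survey comparisons and associations will be analysed with a random GP effect or with GP-cluster-robust standard errors. Where the outcome is clearly non-normal, use cluster-robust or cluster-bootstrap inference in place of the rank tests.

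If the earlier surveys are available only as summary data, multiply the standard error of the new patient-survey estimate by the square root of its estimated design effect before comparing. At a design effect of 2.45 that factor is 1.57. Multiplying by 2.45 itself would overcorrect, because the design effect applies to the variance. Summary data alone will not show whether the earlier surveys were clustered, so that limit should be reported with the comparison.

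The cost is a change of analysis wording, with no change to sampling or data collection; the named software fits mixed models. The downside is somewhat larger p-values and standard errors.

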#### Focus groups (phase I)

Analysis of the transcripts will be conducted by two researchers using the framework method as it allows for a structured approach of the data and easier recognition of patterns [69]. The researchers will first familiarise themselves with the contents of the transcripts and subsequently code parts of the transcript using ATLAS.ti software (v.8.4). The researchers will identify themes using the codes and will review the themes for accuracy in order to identify the relevant theoretical domains.

#### Pilot (phase II)

The semi-structured interviews at the end of the pilot will be performed by a trained interviewer, voice recorded and transcribed verbatim afterwards. Thematic analysis according to the framework method will be performed method as described under *focus groups.*

#### Trial (phase III)

Descriptive statistics will be used to summarize population characteristics. For the primary analysis, the mean NCQ score at baseline and at 12 months follow-up will be compared using a linear mixed model with a random effect for practice and a fixed effect for time point. To analyse if differences depend on longer exposure to the TOOL-kit, the main effect of wedge number and the two-way interaction between wedge number and time point will be determined.

Secondary outcomes measures from the surveys will be compared before and after the intervention and between measurements on different time points using mixed linear models or generalized estimating equations depending on the type of outcome measure. This accounts for clustering of participants within the practices. For outcomes that are collected in more than two periods, the length of exposure to the TOOL-kit main determinant will be considered using the control condition as a reference. A two-sided significance level of 5% will be used for all analyses.

The semi-structured telephone interviews will be analysed according to the framework method described in the *focus groups* section.

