#### Randomisation and blinding

Practices will be randomised to a wedge using computer-generated random numbers in Microsoft Excel 2016 by a researcher from our group. General practices randomised to wedge 1 will start with the intervention immediately after baseline measurement. Practices of wedge 2 will start in the control condition, providing 3 months of usual care before receiving the intervention. Practices of wedge 3 will start in the control condition, providing usual care for 6 months before start of intervention.

Researchers will be blinded to group assignment during data analysis where possible. Due to the study design and nature of the intervention, researchers, GPs and practice assistants cannot be blinded to group assignment.

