#### Sample size

The sample size calculation was based on our primary outcome measure (the NCQ). For both NCQ distribution cycles in month 0 and month 12, we will approach 100 patients per practice. We expect at least 35 patients per practice to participate, resulting in a total of 1050 patients in each cycle. When the mean NCQ score is compared between cycles using a mixed linear model with a random effect for practice and two-sided testing at a significance level of 5%, the expected sample size allows detection of all standardized effect sizes of 0.12 and larger with at least 80% power irrespective of the intra-cluster correlation coefficient. The standardized effect size is defined as the difference in means divided by the total standard deviation incorporating both the between- and within-practice variation.

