#### Data collection

The NCQ will be distributed to patients in month 0 and 12 in all practices (Table 1). The participating general practices will be provided with a selection algorithm for identification of 100 eligible patients from the EMR. Eligibility criteria are: aged 65 or older, registered at the participating general practice, able to speak Dutch or English, community living, no severe cognitive impairment, and at least 1 GP consultation in the past 12 months. Eligible patients will receive a postal invitation for participation together with the questionnaire.

Digital surveys will be distributed to all GPs and practice assistants using Survalyzer at baseline (month 0) and during follow-up at 3, 6, 9, 12, 15 and 18 months. The baseline survey will address barriers and facilitators for implementation related to the practice organisation, structure and working methods. This survey will contain the same questions for all practices. The other surveys will prospectively measure the implementation, acceptability and feasibility, barriers and facilitators of the intervention during the trial. Because the intervention will be tailor-made per practice, each practice will receive surveys containing questions specifically formulated for that practice to ensure optimal data collection and ability to register unexpected events [48].

Two semi-structured telephone surveys will be held with coordinating GPs of all practices within one month and three months after the introduction of the TOOL-kit in that practice. In interview one, the fidelity, acceptability and other barriers for implementation of the TOOL-kit application will be adressed. Interview two will assess the practice improvement plan for personal continuity on the same parameters as interview one. In month 18, a concluding group interview will be held by videoconference per practice with all GPs and practice assistants to conclude the process evaluation.

The interviews will be conducted by a trained interviewer, voice recorded and transcribed verbatim afterwards.

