Phase III and IV of the study will probably take place during the current SARS-CoV-2 (coronavirus) pandemic. Because especially complex interventions interact with the context they are performed in, [73] it is likely that the effect of the intervention will be affected by the coronavirus pandemic. We aim to mitigate this effect by dedicating part of the interviews and surveys in our process evaluation to the influence of the coronavirus on general practice. Additional reminders will be sent to reduce non-response and practices will be contacted periodically to assess trial feasibility within that practice and to tailor design adaptions when necessary and where possible.

All phases of the study will focus on personal continuity in Dutch general practice. Although this increases the relevance of the study results for Dutch clinical practice and healthcare policies, additional translational steps may be required to ensure its relevance in other countries.

In summary, the overall aim of this study is to develop and evaluate a complex intervention for improving personal continuity: the TOOL-kit. We will do this by performing a literature study (phase 0), a survey, focus groups and a Delphi study (phase I) followed by a pilot (phase II) and a cluster randomised stepped wedge pragmatic trial (phase III). We will use the results of phase III to define the conditions for further implementation of the TOOL-kit (phase IV).

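### The primary model has no patient covariates, so a within-practice change in NCQ-related respondent characteristics between month 0 and month 12 would be read as TOOL-kit effect

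*Protocol article*

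**What the plan says.** All statements are in the protocol article.

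- **Analysis, Trial (phase III).** Mean NCQ at baseline and at 12 months is "compared using a linear mixed model with a random effect for practice and a fixed effect for time point". No patient-level term is named. On patient mix the section says only "Descriptive statistics will be used to summarize population characteristics". For length of exposure, "the main effect of wedge number and the two-way interaction between wedge number and time point will be determined".
- **Data collection.** "The NCQ will be distributed to patients in month 0 and 12 in all practices". The mode is postal: "Eligible patients will receive a postal invitation for participation together with the questionnaire". One selection algorithm and one set of eligibility criteria are described.
- **Randomisation and blinding.** Wedge 1 starts directly after baseline and wedge 2 after 3 months. Wedge 3 starts last, "providing usual care for 6 months before start of intervention".
- **Sample size.** 100 patients per practice are approached in each cycle. "We expect at least 35 patients per practice to participate", which gives 1050 per cycle over 30 practices. The detectable standardized effect is 0.12 with at least 80% power, two-sided 5%.
- **Discussion.** Phase III will probably run during the pandemic. The stated measure against non-response is "Additional reminders will be sent to reduce non-response".

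**The concern.** The trial is called a stepped wedge, but on the primary outcome no practice is in the control condition at month 12. At that point the wedges have had 12, 9 and 6 months of exposure. The primary contrast is therefore before against after, and it has no concurrent control that could absorb a change in who replies.

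The random practice effect deals with stable differences between practices. It does not deal with a difference, inside a practice, between those who replied at month 0 and those who replied at month 12. If the later respondents are, for example, older or longer registered, and such patients score differently on the NCQ, the time coefficient carries that difference. The wedge and wedge-by-time terms do not help, because they compare lengths of exposure and contain no information on respondent mix.

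The target effect is small, so a modest bias is a sizeable fraction of it. Eligibility rules that are identical at both cycles do not settle the matter, since about two thirds of those invited are expected not to answer.

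**Working it through.** **1. Reproduce the plan's figure.** Inputs from the Sample size section: 30 × 35 = 1050 respondents per cycle, two-sided 5%, 80% power, total SD set to 1. Treat the cycles as unlinked samples whose shared practice effect cancels in the time contrast:

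SE = √(2(1 − ICC)/1050); detectable effect = (1.960 + 0.842) × SE.

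- ICC 0: SE = √(2/1050) = 0.0436, detectable effect 0.122, power at 0.12 is 78.5%.
- ICC 0.05: detectable effect 0.119, power 80.5%.
- ICC 0.10: detectable effect 0.116, power 82.6%.

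The stated 0.12 is reproduced to rounding. If the same patients were paired, with an assumed correlation of 0.3 to 0.7, the detectable effect would be 0.102 to 0.067. The plan's figure therefore corresponds to two unlinked sets of respondents.

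**2. Bias from a respondent shift.** Let q be the change between cycles in the share of respondents with some characteristic, and d the NCQ difference in SD units that goes with it. The time coefficient is then biased by b = q × d. The documents give neither q nor d, so every value below is an assumption.

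**3. Type I error with no true effect**, at ICC 0:

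P(reject) = 1 − Φ(1.96 − b/0.0436) + Φ(−1.96 − b/0.0436)

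| q (assumed) | d (assumed) | b (SD) | b / 0.12 | P(reject) |
|---|---|---|---|---|
| 0.05 | 0.2 | 0.01 | 8% | 5.6% |
| 0.10 | 0.2 | 0.02 | 17% | 7.4% |
| 0.10 | 0.4 | 0.04 | 33% | 15.0% |
| 0.20 | 0.3 | 0.06 | 50% | 28.0% |

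At ICC 0.05 the four rates are nearly the same: 5.6%, 7.6%, 15.6% and 29.2%.

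**4. Simulation of the mechanism.** The setting was 30 practices × 35 respondents, ICC about 0.05, no true effect, and the deliberately large case q = 0.15, d = 0.5 (300 runs). The stated model gave a mean estimate of 0.075 SD and rejected in 43% of runs. With the characteristic added as a covariate, the mean estimate was 0.000 and the model rejected in 5.0%. With 300 runs the simulation standard errors are about √(0.43 × 0.57/300) = 2.9 points and √(0.05 × 0.95/300) = 1.3 points.

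**5. What the practice effect does absorb.** In an extreme simulated case, only the number of replies per practice changed, with more replies from high-scoring practices at month 12. The raw difference in means was 0.21 SD and the mixed-model estimate 0.05 SD. Most of that kind of change is removed.

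**6. Precision.** If the covariates explained 5–10% of the variance (assumed), the SE would be multiplied by √0.95 = 0.975 to √0.90 = 0.949. That is equivalent to 1/0.95 − 1 = 5% to 1/0.90 − 1 = 11% more respondents.

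**The case against.** The other side has several good arguments.

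- **Scope.** A journal article may leave covariates to an analysis plan that is not shown, and nothing here forbids adjustment. That is true, and an unseen plan may add covariates. But the article does name the terms of the primary model, patient characteristics are not among them, and a better model can be stated at very little cost.
- **The design limits drift.** The practices are the same, one algorithm and one set of criteria are described, and the cycles are 12 months apart, so the season matches. This makes a large shift less likely but does not exclude one at 35% response.
- **The sizes are hypothetical.** This stands. For a characteristic held by half the respondents, chance alone gives an SE of √(2 × 0.25/1050) = 2.2 points for the change in share, and that variation is already in the model's error. A 10-point shift is more than four such SEs, so it would need a systematic cause, and the documents show none of that size.
- **The fix is partial.** This also stands. Response driven by satisfaction with the GP would remain, and so would the confounding of a before-after contrast.

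Stronger readings are tempting and should be resisted. A reader might infer that any change in who answers is counted as effect. Only within-practice changes in characteristics related to the NCQ bias the estimate. A reader might also infer that reminders will differ between cycles, or that different patients are invited at month 12. The article says neither. That the samples are unlinked is an inference from the model and the sample size, although respondents can differ even if the same patients are invited.

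**Conclusion.** The point holds in a limited form and merits a change to the plan. In the stated primary model, a within-practice change in NCQ-related respondent characteristics cannot be told apart from the TOOL-kit effect, because all practices move from untreated to treated between the only two measurements.

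Its size is unknown. Under the assumed shifts the bias ranges from negligible (0.01 SD, type I error 5.6%) to material (0.04–0.06 SD, one third to one half of the 0.12 SD target, type I error 15–28%). These figures rest on assumed q and d, on 1050 respondents per cycle and on unlinked samples. They show sensitivity and do not predict bias in this trial. It would be wrong to conclude that the result will be biased, or that adjustment makes the before-after contrast safe.

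**What to change.** In Analysis, Trial (phase III), define the primary model as a random practice effect and a fixed time point, plus patient age and sex as prespecified fixed covariates. Add time registered with the practice if it is available in the same way at both cycles. Add number of chronic conditions only if it is measured identically at both cycles and judged not to be affected by the TOOL-kit. Do not adjust for consultations in the trial year, which the TOOL-kit can change. Report the unadjusted model as a sensitivity analysis.

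State alongside it that the adjustment removes only measured case-mix differences, and does not deal with unmeasured non-response bias or with secular and pandemic change.

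The cost is a few sentences in the plan, a few extra items on a questionnaire that is sent anyway (or practice record data where these are available), and some missing covariate values. A chronic-condition count would cost more, since it needs record linkage or self-report.

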#### Population and sampling

30 General practices from the Amsterdam (*n* = 15) and Nijmegen (*n =* 15) areas (Fig. 2) will be included. Practices will be included purposefully to comprise a broad spectrum of practice characteristics based on level of urbanisation, practice size and social-economic status of the practice area. [name] and [name] observed that group practices tend to be more at risk for discontinuity (unpublished results, see Additional file 2). Therefore, only general practices employing three or more GPs will be included.

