#### Intervention

The TOOL-kit will be introduced in all participating practices during the course of the study. After receiving the TOOL-kit, practices will be instructed to use it to optimise personal continuity for their older patients. Because the TOOL-kit is introduced on a practice level, all employees and all patients of a practice will be exposed to the intervention. Its introduction is the complex intervention of the study.

The TOOL-kit will consist of multiple components defined in phase 0, I and II. As complex interventions may work best when adapted to local circumstances [48], the TOOL-kit will contain both components which are obligatory and identical for all practices and optional components tailored to the local circumstances of a practice. The components will include professional-oriented strategies (e.g. educational materials, audits and feedback), patient-oriented strategies (e.g. decision aids, arrangements for (direct) contact with healthcare providers) and organisation-oriented strategies (e.g. arrangements for follow-up of patients, revision of professional roles) [58].

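### The primary model has only a random practice intercept, so it assumes all practices change alike between month 0 and month 12; if they do not, the 5% level is not controlled and the stated power does not hold.

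*Protocol article*

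**What the plan says.** The Trial (phase III) part of the Analysis section fixes the primary comparison of baseline with 12 months as a fit "using a linear mixed model with a random effect for practice and a fixed effect for time point". It adds, as a further question about length of exposure, the main effect of wedge and the wedge-by-time-point interaction. The error level is also set there: "A two-sided significance level of 5% will be used for all analyses".

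The Sample size section uses the same model: "When the mean NCQ score is compared between cycles using a mixed linear model with a random effect for practice". It claims "detection of all standardized effect sizes of 0.12 and larger with at least 80% power irrespective of the intra-cluster correlation coefficient". The scale is the total SD: "The standardized effect size is defined as the difference in means divided by the total standard deviation". The design is "30 General practices from the Amsterdam" and Nijmegen areas, and "We expect at least 35 patients per practice to participate, resulting in a total of 1050 patients in each cycle".

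The Intervention section says that the TOOL-kit includes "optional components tailored to the local circumstances of a practice". Under Randomisation and blinding, practices start at month 0, 3 or 6, depending on wedge.

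**The concern.** A single random practice effect induces one correlation between any two patients of a practice, whether they answer in the same cycle or a year apart. The practice deviation then cancels exactly from the month 12 minus month 0 contrast, and about 2,100 patient observations supply the error term.

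If practices drift apart over the year, the deviation does not cancel. What remains is averaged over 30 practices, not 1,050 patients per cycle, and the proper reference is the spread of the 30 practice-level changes, with about 29 degrees of freedom. A model without that term spreads this variation across the patient residual, where it hardly shows. With separate samples the standard error is then too small, the interval too narrow and the 5% level exceeded. This is the trial's one primary test.

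The same assumption sits under the sample size. Power can be independent of the ICC only if the practice effect cancels completely, so the two sections have to be corrected together.

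**Working it through.** **Inputs.** From the protocol: 30 practices, 35 responders per practice and cycle (1,050 per cycle), two cycles, total SD 1, two-sided 5%, effect 0.12. Assumed, because the protocol does not give them: ICC 0.01 to 0.10; CAC (the correlation of a practice's effect between the two cycles) 0.9 or 0.8; overlap of patients between cycles.

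**Step 1: reproduce the stated power.** With a random intercept only, Var(difference) = 2(1 − ICC)/1050. ICC = 0 is the worst case: SE = √(2/1050) = 0.0436. The effect detectable with 80% power is (1.960 + 0.842) × 0.0436 = 0.122, which rounds to 0.12. Power for exactly 0.12 is 78.5% at ICC 0, 80.5% at ICC 0.05 and 82.6% at ICC 0.10. The claim reproduces to rounding, and only on the assumption that the practice effect cancels.

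**Step 2: let practices change differently, separate samples.**
- True variance: 2[(1 − ICC)/1050 + ICC(1 − CAC)/30].
- Variance used by the planned model: 2R/1050, with R = (1 − ICC) + ICC(1 − CAC) × (29 × 35)/2069. The residual has 2100 − 30 − 1 = 2069 degrees of freedom, of which 29 carry the practice-by-time variation, so only about 0.49 of that variance enters R.
- Type I error: 2[1 − Φ(1.96/√ratio)], where ratio = true variance/model variance.

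Example, ICC 0.05 and CAC 0.8: true variance = 2[0.95/1050 + 0.01/30] = 0.002476, SE 0.0498. R = 0.95 + 0.01 × 0.49 = 0.9549; model variance = 0.001819, SE 0.0426. Ratio 1.36; 1.96/√1.36 = 1.68; type I error 9.3%.

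**Step 3: power for 0.12 once the model carries the extra variance.** Power = Φ(0.12/true SE − 1.96). Using 29 degrees of freedom in place of the normal approximation lowers it slightly further.

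| ICC | CAC | True SE | Type I error, planned model | Power for 0.12, corrected model |
|---|---|---|---|---|
| 0.01 | 0.9 | 0.0442 | 5.4% | 77.5% |
| 0.01 | 0.8 | 0.0449 | 5.8% | 76.1% |
| 0.02 | 0.9 | 0.0447 | 5.8% | 76.5% |
| 0.02 | 0.8 | 0.0462 | 6.6% | 73.8% |
| 0.05 | 0.9 | 0.0463 | 7.1% | 73.6% |
| 0.05 | 0.8 | 0.0498 | 9.3% | 67.4% |
| 0.10 | 0.9 | 0.0488 | 9.5% | 69.1% |
| 0.10 | 0.8 | 0.0552 | 13.9% | 58.5% |

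At ICC 0.05 the effect detectable with 80% power becomes 0.130 (CAC 0.9) or 0.139 (CAC 0.8).

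**Step 4: simulation check, separate samples.** Simulated type I error of the planned test was 7.1% (ICC 0.05, CAC 0.9), 9.4% (0.05, 0.8) and 13.6% (0.10, 0.8). At CAC 1 it was 4.9%, so the omitted term is the sole cause of the inflation. A practice-level test of change with 29 degrees of freedom, equivalent in this balanced design to adding the term, gave 4.8–5.3%.

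**Step 5: the same patients in both cycles, pairing ignored.** With a fraction o of responders repeated and an assumed within-patient correlation of 0.5, the first part of the true variance becomes (1 − ICC)(1 − 0.5o)/1050. At ICC 0.05 and full overlap:
- CAC 0.9: true variance 2[0.475/1050 + 0.005/30] = 0.001238 against a model variance of 0.001814; ratio 0.68, type I error 1.8%.
- CAC 0.8: 2[0.475/1050 + 0.01/30] = 0.001571 against 0.001819; ratio 0.86, type I error 3.5%.

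At half overlap the figures are 4.2% and 6.3%. At ICC 0.10, CAC 0.8 and full overlap it is still about 8%.

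**The case against.** A reader might infer that the planned test is simply anti-conservative. The protocol does not support that as an unconditional statement. Inflation needs a non-trivial ICC, a CAC below 1 and limited patient overlap, and none of the three is given. At ICC 0.01 the excess is under one percentage point. If the same patients answer twice, ignoring the pairing can make the test conservative. Separate samples are the natural reading, since 100 patients per practice are approached in each cycle and no patient effect or linkage is mentioned, but the protocol does not say so. This part stands, and it is why the size is given as a range.

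The reasons for expecting unequal change also need care. Tailoring makes treatment effects differ between practices. If the TOOL-kit did nothing anywhere, tailoring could not inflate type I error; it bears on the coverage of the interval for an average effect. The Discussion expects the pandemic to affect the intervention's effect, but does not say that practices will be affected unequally. Staffing change is described as a general trend in the Background, not as a feature of the trial practices. These points weaken the argument for large practice-by-time variance. They do not justify fixing it at zero.

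Two other defences fail. The wedge-by-time interaction is a fixed effect in a further analysis; it captures mean differences between three wedges, not variation between practices within them. Nor is this detail left to an analysis plan: the protocol states the model, and its power claim holds only under that model's assumption.

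**Conclusion.** The point holds in conditional form. The stated primary model assumes equal change in every practice. If that fails, the 5% level is not controlled. With separate samples the error is upward: about 5–6% at ICC 0.01, 6–7% at 0.02, 7–9% at 0.05 and 10–14% at 0.10, for CAC 0.9 to 0.8. With full overlap, an assumed within-patient correlation of 0.5 and ICC 0.05 it is about 2–4%, so even the direction is not settled by the document. A landing near 5% through two omissions that offset each other would not be error control.

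The claim that power is unaffected by the ICC falls with the same assumption. With separate samples, power for 0.12 is about 74%, 67% and 58% at (ICC, CAC) of (0.05, 0.9), (0.05, 0.8) and (0.10, 0.8). All ICC, CAC and overlap values are assumptions.

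**What to change.** 1. In the Trial (phase III) analysis, add a random practice-by-time-point effect to the primary model and test the time effect with Satterthwaite or Kenward-Roger degrees of freedom.
2. State whether the month 12 sample may include month 0 responders. Where the same patient answers in both cycles, link the answers and add a random patient effect.
3. In the Sample size section, replace the claim that power does not depend on the ICC with power, or the detectable effect, over a stated range of ICC and CAC, so that both sections describe one model.

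The cost is an extra random term or two, a few sentences, and linkage of repeat responders; no extra questionnaires are needed. The real price is a wider interval where practices change differently and a less favourable stated power. The change does not make the contrast an estimate of the TOOL-kit's effect: all practices are measured only at months 0 and 12, so the comparison stays confounded with calendar time, which is a separate matter.
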